#### Economic analysis

The economics analysis will take an NHS and personal social services cost perspective in accordance with National Institute of Health and Care Excellence (NICE) guidance, including medication, inpatient and outpatient hospital visits and primary and community care use. It will also take a wider societal perspective to capture the broader effects of rTMS and cgiTBS on depression such as paid employment, caring responsibilities and other implications for friends and family. Resource data will then form the units on which cost data, using sources such as the Unit Cost of Health and Social Care\Personal Social Services Research Unit (PSSRU),^39^ the British National Formulary and national reference costs can be attached. The nurse and healthcare assistant at each centre will complete a diary of time spent managing each participant in the RCT to derive treatment costs for rTMS and cgiTBS. The number of treatment sessions for each treatment arm will be carefully recorded and a separate intervention cost assigned to each of the therapies. We will delineate the time spent delivering cgiTBS or rTMS from time spent on research only procedures, such as imaging for delivery of rTMS and additional mechanistic scans in both treatment arms or the extended length of the TBS session for blinding that would not be used in the real clinical world. The outcome measure for the economic evaluation will be the number of quality-adjusted life year (QALY) based on a 6-month time horizon with no discounting for costs or outcomes as they accrue within a 12-month period. An incremental analysis will be used between the two groups and where appropriate an incremental cost effectiveness ratio will be reported between rTMS and cgiTBS. We will use the net monetary benefit framework and implement a net benefit regression,^40^ to estimate the extent to which, and the probability that, the cgiTBS intervention is cost-effective compared with standard rTMS at a range of threshold values for the willingness to pay per QALY, generating cost-effectiveness acceptability curves. Data will be analysed for baseline and centre effects. Key cost drivers will be examined using probabilistic sensitivity analysis.

#### Qualitative analysis

A purposive sample of 25–30 participants from both arms and all centres, reflecting a mix of demographic characteristics, consent or non-consent to participate, adherence and non-adherence to treatment and follow-up will be selected for qualitative interviews, each lasting for up to an hour, after the 16 weeks assessment (the primary outcome). We will ask about their general views of TMS, benefits from, disadvantages from or dislikes about receiving TMS. Interviews will continue until theme saturation is achieved, that is, no more themes emerge in subsequent interviews. Qualitative interviews of barriers to recruitment, with staff members involved in recruitment, will also be completed to optimise strategies to improve recruitment as the RCT proceeds. All interviews will be recorded and transcribed verbatim. Inductive thematic analysis using a grounded approach will be adopted.

### Sample size

Sample size is calculated on the minimum clinically important difference in responder rates from baseline to 16 weeks of 15% (equivalent to a number needed to treat of 7) between two active treatments (cgiTBS vs rTMS) in favour of the experimental condition cgiTBS. This is an effect size regarded in the literature as a clinically important difference in studies using invasive approaches to manage TRD such as vagal nerve stimulation.^40^ The most recent meta-analysis of 16 RCTs in 977 participants with TRD reports a response rate on the HDRS-17 and the Montgomery-Åsberg Depression Rating Scale of 26.5% for rTMS at the end of treatment vs 13.1% for sham TMS.^6^ Assuming a response rate on the HDRS-17 of 26.5% with rTMS and 41.5% with cgiTBS, 368 patients in total (184 per arm) will provide a power of 80% to detect the difference in response rates at a 5% significance level (two tailed), allowing for 15% lost to follow-up at 16 weeks.^6^

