Therefore, in a small pilot study of 27 TRD patients,^21^ individualised left DLPFC targets were determined using Granger causality analysis (GCA) to provide a measure of effective functional connectivity (eFC) seeded from the rAI. Of the 18 participants who completed all follow-up in the two treatment arms (connectivity guided rTMS (cgrTMS) and cgiTBS) higher response rates were found at 3-month follow-up favouring cgiTBS (89%) over cgrTMS (44%), indicating the potential for longer lasting efficacy of cgiTBS.

In addition, rsfMRI and MR spectroscopy (MRS) may advance neuromodulation therapy through mechanistic evaluation of effects and response predictions. iTBS may dampen fronto-insular eFC in responders with TRD.^21^ Left DLPFC gamma-aminobutyric acid (GABA) levels are increased significantly in rTMS responders versus non-responders.^22^ In addition, DLPFC targeted TMS normalises dysfunctional fronto-limbic networks in TRD, with decreased hyperconnectivity between the subgenual anterior cingulate cortex (ACC), ventromedial and dorsomedial prefrontal cortex and DLPFC.^23^ iTBS may induce widespread and longer-term network change but precise anatomical localisation of the target circuitry may be required for maximal efficacy of iTBS to normalise dysfunctional fronto-limbic circuitry. Such changes may increase the proportion of people with TRD who obtain a sustained response compared with neuronavigated rTMS. Thus, this multicentre RCT will examine the clinical and cost-effectiveness of cgiTBS in comparison with neuronavigated rTMS, in treatment-resistant moderate to severe MDD.

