### Statistical analyses

#### Efficacy analysis

The primary analysis will test the null hypothesis that treatment with cgiTBS does not increase response rate as measured by HDRS-17 compared with rTMS at 16 weeks on an intent to treat population with any missing response data at 16 weeks being imputed as no response having been achieved. Response at 16 weeks was selected as the primary outcome because of the much larger response rate with cgiTBS than rTMS in our pilot study.^21^ A logistic regression will be fitted for the outcome of response with treatment arm, centre, baseline HDRS-17 score and MGH TRD score.

As a secondary analysis a logistic regression model will be repeated in completers (those with 10 or more rTMS or cgiTBS treatments, assessed at baseline and 16 weeks) and a per-protocol analysis. Secondary outcomes are the and proportion of responders and remitters at 8, 16 and 26 weeks, and sustained responders at both 16 and 26 weeks will be compared between groups using logistic regression adjusted for treatment centre, baseline HDRS-17 score and MGH TRD score (5% significance). All outcomes are shown in table 3. Repeated measure linear models will be used for continuous outcomes. Patient acceptability (5-point scale) and safety of both cgiTBS and rTMS (side-effects checklist) will be reported descriptively.

**Table 3 T3:** Study efficacy outcome measures

Outcomes	Measure	Time points
Primary Outcome	17-Item Hamilton Depression Rating Scale (HDRS-17)	Response at 16 weeks (defined as by a 50% or greater reduction in HDRS-17 score from baseline)
Secondary Outcomes	HDRS-17	Mean change in HDRS-17 score compared with baseline at 8, 16 and 26 weeks Response (as defined above) at 8 weeks and at 26 weeks Sustained response at 16 and 26 weeks (defined as a continuing response as defined above following a response at the previous time point) Remitters at 8, 16 and 26 weeks (defined as a score of 7 or less on the HDRS-17)
	Beck Depression Inventory-II	At 8, 16 and 26 weeks
	Patient Health Questionnaire Quick Inventory of Depressive Symptomatology	At 8, 16 and 26 weeks At 8, 16 and 26 weeks
	Generalised Anxiety Disorder Assessment	At 8, 16 and 26 weeks
	THINC Integrated Tool	At 8, 16 and 26 weeks
	EuroQol-five-Dimensions-five-Level	At 8, 16 and 26 weeks
	Work and Social Adjustment Scale	At 8, 16 and 26 weeks
	Patient Acceptability (1–5 scale)	After each TMS session and at 8, 16 and 26 weeks
	Adverse Events Checklist	After each TMS session and 8 weeks

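### The stated 80% power takes the 15% lost to follow-up out of the analysis, but the primary analysis keeps them as non-responders: 184 per arm gives about 77% or about 86%, depending on what the assumed rates mean

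*Protocol article*

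**What the plan says.** **Sizing (Sample size).** The target is a "minimum clinically important difference in responder rates from baseline to 16 weeks of 15" percentage points. The inputs are given as "Assuming a response rate on the HDRS-17 of 26.5% with rTMS and 41.5% with cgiTBS", tested two-sided at 5%. The result is that "368 patients in total (184 per arm) will provide a power of 80% to detect the difference in response rates", "allowing for 15% lost to follow-up at 16 weeks". The control rate comes from a meta-analysis, reported as "26.5% for rTMS at the end of treatment vs 13.1% for sham TMS".

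**Analysis (Efficacy analysis).** The primary comparison of week-16 response is by intention to treat, with "any missing response data at 16 weeks being imputed as no response having been achieved". It is a logistic regression on arm, centre, baseline HDRS-17 and the MGH treatment-resistance score. The outcome definition under Study schedule has the same rule: a patient with no week-16 value is a non-responder.

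The article does not say whether the assumed 26.5% and 41.5% are rates among assessed patients or rates with missing patients already counted as failures.

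**The concern.** Dividing an evaluable sample size by one minus the loss rate suits an analysis restricted to patients with data: the number analysed falls and the response rates stay as assumed. Under non-responder imputation the number analysed does not fall. Missing patients stay in the denominator and cannot be responders, so both response rates shrink, and the difference between them shrinks with them. The allowance for loss in the sizing section and the handling of loss in the primary analysis are thus two different mechanisms, and the quoted power belongs only to the first.

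At stake is how the result is read. A non-significant finding will be weighed against a claimed 80% chance of detecting 15 points. If the rates are those among assessed patients, the primary analysis is looking for a smaller difference with somewhat less power, and power falls further as attrition rises.

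**Working it through.** **Inputs.** From Sample size: p1 = 0.265, p2 = 0.415, two-sided alpha 0.05, power 0.80, loss 15%, 184 per arm. From Randomisation: 1:1 allocation. From Efficacy analysis and Study schedule: missing at week 16 = non-response.

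**1. Reproduce the plan's figure.** Pooled-variance two-proportion formula without continuity correction, with p̄ = 0.34:

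n = [1.960·√(2·0.34·0.66) + 0.842·√(0.265·0.735 + 0.415·0.585)]² / 0.15² = 155.4, so 156 per arm (power 80.2%).

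156 / 0.85 = 183.5, so 184 per arm and 368 in total. This is an exact match. Other common formulas do not reproduce it after inflation: about 180 unpooled, 182–183 arcsine, 199 with continuity correction. The stated 80% is therefore the power with 156 analysed per arm at the undiluted rates.

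**2. Apply the primary analysis, taking the rates as those among assessed patients.** With 15% missing in each arm:

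- rTMS: 0.85 × 0.265 = 0.22525
- cgiTBS: 0.85 × 0.415 = 0.35275
- difference: 0.1275

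With 184 per arm and p̄ = 0.289:

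- standard error under the null = √(2·0.289·0.711/184) = 0.0473
- standard error under the alternative = √((0.1745 + 0.2283)/184) = 0.0468
- power = Φ[(0.1275 − 1.960·0.0473)/0.0468] = Φ(0.745) = **77.2%**

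Other methods at the same inputs give 77.8% (unpooled), 77.5% (exact power of the chi-square test) and 76.4% (Wald test of the log odds ratio). On this reading, 80% would need 198 per arm (396 in total).

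**3. Sensitivity to missingness on this reading (184 per arm, equal loss in both arms).**

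| Missing | Power |
|---|---|
| 5% | 83.5% |
| 10% | 80.5% |
| 15% | 77.2% |
| 20% | 73.6% |

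**4. Why the loss of power is small.** Compared with 156 per arm at 26.5% vs 41.5%, three things change:

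- the squared effect is multiplied by 0.85² = 0.7225;
- the number analysed is multiplied by 184/156 = 1.18;
- the lower rates reduce the summed variance from 0.4376 to 0.4028, a factor of 1.086 in information.

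The product is about 0.93, so about 93% of the intended information remains.

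**5. The other reading: the rates already count missing patients as failures.** All 184 per arm are then analysed at 26.5% vs 41.5%:

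power = Φ[(0.15 − 1.960·0.0494)/0.0488] = Φ(1.09) = **86.2%**

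No inflation was needed, because 156 per arm already gives 80.2%. At 15% missing, this reading implies 0.265/0.85 = 31.2% and 0.415/0.85 = 48.8% among those assessed, a difference of 17.6 points.

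**The case against.** The strongest reply is that the primary outcome is itself defined with missing as non-response, and that the 15-point target is set on responder rates for that outcome. Read literally, 26.5% and 41.5% are then rates on the imputed scale, power is 86%, and the inflation is merely conservative. This cannot be ruled out, because the article does not say how the source of 26.5% handled dropouts. It stands to this extent: 77% must not be presented as the trial's unconditional power. It does not rescue the 80%, which is then also wrong, though in the favourable direction.

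Second, the calculation is unadjusted, while the model includes centre and two baseline scores. From step 4, a gain in information of about 8% (1/0.93) would close the gap. The article quantifies no such gain, so it cannot be credited, but this shows how small the gap is.

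A reader might also infer more than the text supports:

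- **That attrition could reach one third.** The pilot had 27 patients, and the report is given as "Of the 18 participants who completed all follow-up in the two treatment arms", 18 in number. The article does not say that all 27 entered those two arms, or that nine lacked the 3-month outcome.
- **That the week-16 control rate may be nearer 44%.** That pilot figure is for connectivity-guided rTMS, not this trial's comparator, and comes from completers in a sample of 18 across two arms.
- **That an end-of-treatment control rate must overstate power.** The article openly labels 26.5% as such. Its remark that rTMS benefit may last only 1–3 months points to a lower rate at week 16, which is 10–12 weeks after a 4–6 week course. With a fixed 15-point difference and 15% missing, a 20% control rate gives 82.6%, which is above 80%.

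**Conclusion.** The point holds as a mismatch between the sizing section and the primary analysis. The 80% is reproduced only with lost patients removed, whereas the plan keeps them and scores them as non-responders. At the planned 15% loss, power for 184 per arm is about 77% if the assumed rates are those among assessed patients, and about 86% if they already include missing as non-response. The first is what inflating for loss implies, but the article does not settle it.

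The 77% further rests on equal loss in the two arms and on no gain from covariate adjustment. It would be too strong to say that the trial never had the stated power: that is false on the second reading, and on the first, power is 80.5% if missingness stays at 10%. The shortfall is about 3 points at worst under the planned assumptions. It should be corrected, but it does not threaten the design.

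**What to change.** In Sample size:

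1. State whether 26.5% and 41.5% are rates among assessed patients or rates with missing counted as non-response.
2. Restate the power for 184 per arm to match. Either: about 77% at 15% missing per arm, with an analysed contrast of 22.5% vs 35.3% (12.75 points). Or: about 86%, with a note that the assumed rates already absorb the loss.
3. On the assessed-patient reading, add one line of sensitivity: 80.5%, 77.2% and 73.6% at 10%, 15% and 20% missing. Say that these ignore covariate adjustment.
4. Label 26.5% as an end-of-treatment rate carried to week 16 by assumption.

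The cost is a few sentences. Neither the sample size nor the primary analysis has to change. On the assessed-patient reading, the only price is a slightly less favourable stated power.

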### Blinding

Patients, referring clinical teams and the outcomes assessors will be kept blind with respect to the treatment protocol assigned and administered. Any unintended unblinding of outcome assessors will be recorded and another assessor will complete all further assessments for that participant. At each assessment, the outcomes assessor will be asked to guess the treatment allocation of the participant.

## Ethics and dissemination

### Ethical considerations

Ethical approval was granted by East Midlands Leicester Central Research Ethics Committee (ref: 18/EM/0232) on 30/08/2018. The study was registered on 02/10/2018 (ISRCTN19674644) under the public title ‘BRIGhTMIND: brain imaging guided transcranial magnetic stimulation in depression’. The first participant was randomised on 22 January 2019. Study finish is scheduled for September 2021. Overview of the study is performed by an external independent Data Monitoring Ethics Committee reporting to a Trial Steering Committee.

Expenses will be covered for participation in the study along with a £10.00 shopping voucher at 16 and 26 weeks follow-up assessments as a mark of respect and gratitude for the time and input of the participants to the follow-up aspects of the trial.

### Safety considerations

Internationally agreed definitions of adverse events (any untoward medical occurrence in a clinical trial subject administered TMS whether or not it has a causal relationship with TMS) and serious adverse events (any adverse event or adverse reaction that results in death, is life-threatening, requires hospitalisation or prolongation of existing hospitalisation, results in persistent or significant disability or incapacity, or is a congenital anomaly or birth defect). All participants will be asked about adverse events after every treatment (immediately and a maximum of 72 hours later) until they are resolved. Any participant found to be at risk to themselves (suicide, neglect) or others, or developing a serious adverse event will be referred to relevant clinical services. A review by a clinical expert in TRD will be offered to any participant whose depression has become more severe at 16 and 26 weeks for safety reasons.

### Dissemination

All participants will be sent a report summary of the results. Results of the study will be published in peer-reviewed academic journals and communicated widely to academic, profession and public audiences through conferences, media and social media.

## Patient and public involvement

Regarding this study a coproduction approach has been taken. We worked with the Involvement Centre at Nottinghamshire Healthcare Trust to create a Magnetic Stimulation Advisory Group who co-produced the treatment pathway for prior pilot work^21^ and the current study.

During the study, each centre will be invited to contribute at least two patient and public involvement (PPI) representatives to form a Lived Experience Advisory Panel (LEAP) who will contribute to all study meetings and a representative will be invited to attend all research meetings. At each site PPI representatives will seek opinions, test ideas and gain support for the study. Participant information sheets and other study materials will be codesigned. They will see oversee the interpretation of our findings, particularly the emerging qualitative analysis on barriers to recruitment and patient acceptability of TMS. The PPI process will be overseen by an experienced PPI lead who has trained supported and mentored many PPI groups over recent years. The voice of experts by experience will be heard in all dissemination activities, including presentations or publications.

## Discussion

Although TMS is an established efficacious and safe treatment approach for TRD, research is required to establish if it is possible to increase the proportion of people with TRD who derive a sustained improvement in depression response.^8^ Based on theoretical and preliminary empirical evidence, this study explores the potential of using precise personalised neuroanatomical stimulation at a site where affective, cognitive control and default mode networks overlap in neuroanatomical space as determined by MRI derived maximal strength of connectivity between the rAI and the left DLPFC. It will be compared with standard rTMS in a large multicentre RCT. Both rTMS and iTBS are effective against sham treatments^6 8 10^ and recommended for clinical practice in the UK.^8^ Furthermore, standard iTBS is non-inferior but not superior to rTMS.^12^ Thus, if the current RCT showed that cgiTBS was superior in efficacy, it would be reasonable to conclude that the increased efficacy was due to the personalisation of the site of iTBS treatment.

The design of the trial aims to have high external validity and generalisability to inform routine clinical care. Therefore, inclusion and exclusion criteria are broad and confined to ensuring that safety, efficacy and the investigation of mechanism of action are not compromised. Our definition of TRD^26^ is one of the most widely used but it does not consider psychological treatment and underestimates treatment resistance in those who refuse or are not offered antidepressants or ECT in the current episode because of lack of effectiveness or intolerance in previous depression episodes. The broad inclusion and exclusion criteria, large sample size, inclusion of clinical and MRI variables and long duration of follow-up will permit a wide variation in potential predictors and non-predictors of response for clinical practice and further research.

Compromises have been made to the design of the study to improve blinding. cgiTBS and rTMS have been matched procedurally so both use the same MRI and neuronavigation system, although these are not currently being used in clinical practice in UK. TMS treatments have also been matched in terms of pulses received and duration of treatment, although the duration of cgiTBS is delivered over a much longer duration but at a lower motor threshold than the United States Federal Drug Agency protocol used in the Three-D study.^12^ We decided to use the motor threshold that was well tolerated in our pilot study.^21^ We also did not include a third arm of cgrTMS because our pilot study showed a short duration of response similar to standard rTMS.^21^ The use of sham coils to mask the sound and sensation of iTBS and rTMS was explored but effective shams were not available. As a result, entry into the study is restricted to people who had never previously received TMS.

A coproductive approach has been taken with our patient and public LEAP group and this has been particularly important around informing participants accurately about the study and managing participant expectations. By doing this we hope to optimise recruitment and retention to the study.

In many countries, 3 Tesla MRI is increasingly available so that cgiTBS could be implemented into routine care for TRD. Should the RCT demonstrate that cgiTBS is clinically effective at 16 weeks and cost-effective compared with rTMS, then the possibility of maintaining participants with one full course of cgiTBS with booster sessions two or three times per year using the same site of stimulation from a baseline MRI might be feasible. If it is not effective, then other parameters of delivering TMS should be the focus of research and development.

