**Trial registration number:**

ISRCTN19674644

Strengths and limitations of this studyLarge multicentre randomised controlled trial of connectivity guided theta burst stimulation intermittent (TBS) versus standard repetitive transcranial magnetic stimulation (rTMS).Carefully characterised population of patients with treatment-resistant moderate to severe unipolar major depression with broad inclusion and exclusion criteria to enhance generalisability to clinical care.Explores efficacy, sustainability of treatment response, acceptability, cost-effectiveness cognitive function, mechanism of action using MRI and spectroscopy, and clinical and MRI predictors of response in the same sample.Unable to completely blind sound and sensation of the treatments being tested.Both nature of magnetic stimulation (TBS vs rTMS) and stimulation site identification vary between treatment arms.

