### Interventions

For all treatments, a 70 mm figure-of-eight coil (E-z Cool coil) and a Magstim Horizon Performance Stimulator with StimGuide Navigated TMS Package (Magstim Company, Whitland, UK) will be used. Participants in both treatment arms will receive neuronavigation-guided single coil stimulation for 20 TMS sessions delivered over 4–6 weeks. A total of 3000 pulses will be delivered in each rTMS or cgiTBS session. Each treatment session, irrespective of treatment arm, is designed to last approximately 37.5 min in total for the purposes of blinding the participants and assessors of outcome. There must not be a gap of more than 4 days between treatments in the course of 20. Medication will be unchanged over 16 weeks follow-up unless there is clinical risk of harm.

Individuals assigned to cgiTBS will receive bursts of three pulses (80% motor threshold) at 50 Hz applied at a frequency of 5 Hz (ie, every 200 ms) for 40 s duration over a site determined from the assessment of maximal strength of effective connectivity between the rAI and the left DLPFC from fMRI and structural MRI. Neuronavigation computes the nearest location for TBS stimulus on the scalp from an individualised head model based on structural MRI and three fiducial points, the nasion, left preauricular and right preauricular sites. If this site causes discomfort to the participant, it is moved by 1 cm in any direction until there is no discomfort. The pulses are repeated for a total of 5 runs with 5 min rest intervals between runs.

Individuals assigned to rTMS will follow the standard US Food and Drug Administration approved protocol. The site of stimulation will be determined using structural and fMRI utilising neuronavigation to compute the F3 electrode site over the left DLPFC for TMS stimulation from the same head model and three fiducial points. Stimulation is at 120% motor threshold with 75×4 s trains of 10 Hz interspersed by 26 s intertrain intervals.

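### The Discussion would credit superiority of cgiTBS to personalising the site, but the arms also differ in pulse pattern and intensity, so only a package conclusion is supported

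*Protocol article*

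**What the plan says.** The relevant statements in the protocol article are these.

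- **Discussion, planned interpretation.** If cgiTBS is superior, "it would be reasonable to conclude that the increased efficacy was due to the personalisation of the site of iTBS treatment". The reason given is that standard iTBS has been shown non-inferior, though not superior, to rTMS.
- **Strengths and limitations list.** "Both nature of magnetic stimulation (TBS vs rTMS) and stimulation site identification vary between treatment arms".
- **Interventions.** cgiTBS gives "bursts of three pulses (80% motor threshold) at 50 Hz applied at a frequency of 5 Hz", at the individual site of strongest effective connectivity between the right anterior insula and the left DLPFC. For rTMS, "Stimulation is at 120% motor threshold with 75×4 s trains of 10 Hz interspersed by 26 s intertrain intervals", at the F3 site found by neuronavigation. Pulse count is matched: "A total of 3000 pulses will be delivered in each rTMS or cgiTBS session".
- **Discussion, relation to the cited trial.** The cgiTBS here is "delivered over a much longer duration but at a lower motor threshold than the United States Federal Drug Agency protocol used in the Three-D study".
- **Discussion, omitted arm.** There is no connectivity-guided rTMS (cgrTMS) arm because "our pilot study showed a short duration of response similar to standard rTMS".
- **Introduction, pilot.** Both pilot arms were connectivity guided. Among 18 completers, response at 3 months was 89% with cgiTBS and 44% with cgrTMS.
- **Efficacy analysis.** The 16-week endpoint is justified by the pilot difference, with the comparator there called simply rTMS.

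**The concern.** The article commits in advance to a causal reading that its own limitation list argues against. A two-arm trial that changes site, pattern and intensity together estimates the effect of changing all three. It cannot say which of them produced a difference.

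This matters for how the result would be used. The Discussion links a positive result to routine use of cgiTBS, given growing access to 3 Tesla MRI. Whether individual imaging is the active ingredient bears on whether that imaging is needed. The same ambiguity affects a null result, which could reflect any of the three differences or opposing effects among them.

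**Working it through.** **1. The plan's own figure.** Inputs from Sample size: 26.5% versus 41.5%, two-sided 5%, 80% power, 15% loss. The usual two-proportion formula without continuity correction is

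n = [1.96·√(2·p̄·q̄) + 0.8416·√(p₁q₁ + p₂q₂)]² / (p₂ − p₁)²

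With p̄ = 0.34: [1.96·√0.4488 + 0.8416·√0.43755]² / 0.0225 = 155.4, so 156 per arm. Then 156 / 0.85 = 183.5, so 184 per arm and 368 in total. The stated size is reproduced, and it is sized for the package contrast.

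**2. What is matched and what is not (Interventions).**

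| | cgiTBS | rTMS | Same? |
|---|---|---|---|
| Pulses per session | 5 runs × 40 s × 5 bursts/s × 3 = 3000 | 75 × 4 s × 10 Hz = 3000 | yes |
| Sessions | 20 | 20 | yes |
| Nominal session length | about 37.5 min | about 37.5 min | yes |
| Target | individual connectivity site | F3 | no |
| Pattern | triplets at 50 Hz, repeated at 5 Hz | 10 Hz trains | no |
| Intensity (motor threshold) | 80% | 120% | no (ratio 1.5) |
| Active stimulation time | 5 × 40 = 200 s | 75 × 4 = 300 s | no |

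**3. What the contrast contains.** Write R for the 16-week response proportion. Then

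R(cgiTBS) − R(rTMS) = [R(cgiTBS) − R(same iTBS at F3)] + [R(same iTBS at F3) − R(rTMS at F3)]

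The first bracket is the effect of personalising the iTBS site, which is what the Discussion wants to claim. The second is the effect of stimulation type. No participant receives iTBS at F3, so only the sum is estimated. The attribution requires the second bracket to be zero or less, and that must come from outside the trial.

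**4. Whether the cited trial supplies it.**

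- Non-inferiority without demonstrated superiority leaves room for a positive difference. The article gives neither margin nor interval, so the room left cannot be computed from it.
- The Introduction reports that result for reduction in symptoms. The primary outcome here is the proportion with a 50% reduction.
- The Discussion says the iTBS here differs from that trial's in duration and motor threshold. The cited comparison is therefore not the second bracket.

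**5. What a nonzero second bracket would do.** Suppose, for illustration only, that site has no effect and stimulation type alone raises response from 26.5%. With 156 evaluable per arm, the chance of a significant result is:

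| Effect of stimulation type | Power |
|---|---|
| 5 points | 16% |
| 10 points | 48% |
| 15 points | 80% |

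**6. What the pilot adds.** Assuming 9 completers per arm, 89% and 44% are 8/9 and 4/9. With 12 responders among 18, the upper-tail probability is [C(12,8)·C(6,1) + C(12,9)] / C(18,9) = (2970 + 220) / 48620 = 0.0656. The two-sided Fisher p is 0.13. Guidance was present in both arms, so this comparison contains no contrast of guided with unguided stimulation.

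**The case against.** The strongest reply has four parts.

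- **The sentence is a conditional remark in a Discussion.** It is not a hypothesis, an estimand or an analysis. The primary objective, primary analysis and sample size all compare cgiTBS with rTMS as delivered. This stands, and it limits the point to interpretation.
- **The confounding is disclosed.** The limitation list names both pattern and site, and the Discussion volunteers the lower motor threshold and the missing cgrTMS arm. This stands in part. The limitation list does not mention intensity, and disclosure does not remove the conflict with the attribution sentence.
- **The cited trial is relevant indirect evidence.** It followed patients to 12 weeks after 4–6 weeks of treatment, or 16–18 weeks in all, close to this trial's endpoint. It makes a large pattern effect less plausible. It does not show a zero effect for the protocol used here.
- **Guidance may matter specifically for iTBS.** The Introduction suggests that precise localisation may be needed for iTBS to work best. That is a coherent hypothesis, but testing it needs unguided iTBS, which no arm provides.

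A reader might go further and infer from the pilot that guidance adds nothing and that pattern is the cause. The documents do not support this. With guidance in both arms and 18 completers, the pilot cannot show whether guiding iTBS helps. The remark that cgrTMS resembled standard rTMS concerns duration of response and guidance added to rTMS.

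**Conclusion.** The attribution in the Discussion is not supported by the design. The trial can show whether cgiTBS as a package beats neuronavigated rTMS at 16 weeks. It cannot assign a difference, or its absence, to personalisation, pattern or intensity. The cited non-inferiority result weakens the rival explanations but does not exclude them, and the pilot supports neither side of the attribution.

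The share of any difference due to site is not identified. It should not be described as lying between 0% and 100%, because the components could act in opposite directions. The power figures above rest on assumed splits and on the article's own planning rates, and the Fisher result assumes 9 completers per arm.

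A reader might also infer that the primary comparison is compromised. It is not: the hypothesis, its test and the 368 participants are unaffected. No stimulation parameter is judged here.

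**What to change.** 1. In the Discussion, delete the attribution sentence or restate it. Superiority, or its absence, would be concluded for the cgiTBS package versus neuronavigated rTMS and not assigned to personalisation, pattern or intensity. This brings it into line with the limitation list.
2. In Efficacy analysis, name the pilot comparator as cgrTMS, as the Introduction does.

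Both are wording changes, best made before results are known. The cost is a less ambitious claim.

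An optional extra is an exploratory analysis of response against the distance from the stimulated site to the individual connectivity target. It would be informative mainly in the rTMS arm, since distance under cgiTBS is close to zero by design. It would be observational, with about 184 × 0.265 = 49 expected responders at the planning rate. It cannot isolate the effect of guiding iTBS and should not be offered as a substitute for the restated conclusion.
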